### Data Analysis

The primary analysis is the change in systolic blood pressure (SBP) from baseline to 12 months. Meta-analyses have found that for a given blood pressure, SBP predicted over 90% of the risk of ischemic heart disease and stroke and that a 2 mm Hg decrease in SBP could reduce stroke and ischemic heart disease mortality [46]. Analysis will fit a linear regression model with the outcome of 12-month SBP, including baseline SBP and a binary predictor of Unite care model patient (yes vs no) as independent variables.

Other secondary analysis end points will include determining whether functional and cognitive limitations are associated with care model usage, change in physical and social environment, and moves out of the Unite clinic building. To determine if functional and cognitive limitations, including activity limitations and AD/ADRD are associated with Unite care model usage, the research team will build a logistic regression model predicting Unite utilization, including age, sex, race, ethnicity, AD/ADRD status, level of functional disability, self-reported health, and baseline hypertension as independent variables. Change in physical and social environment (item counts) will be assessed using a Poisson regression with an outcome of 12-month values, adjusting for baseline values and including an intervention indicator. Moves out of the clinic building will be assessed by comparing moves out of the building in the 2 years prior to the Unite care model compared to year 2 of the Unite care model.

Of the 300 older adults residing in the Unite building, we estimate that 5% will elect not to enroll, resulting in a study population of 285 older adults. We estimate that we will have 89% power to detect a 2-point change in SBP within older adults assuming a mean baseline SBP of 162 mm Hg and SE of change in SBP over time of 10 mm Hg, based on prior data in this community and community studies [47,48], and a 10% loss to follow-up using an analogous test to our primary analysis. If loss to follow-up increases to 20%, power to detect a 2-point change in SBP would decrease to 85%. The effect may be larger. We will have 100% power to detect a 4-point SBP change if loss to follow-up were 20%.

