**Methods:**

We will assess the care model using a concurrent, exploratory mixed methods design. For aim 1, acceptability will be assessed through semistructured interviews with key stakeholder groups; adoption and penetration will be assessed using housing and health care records. For aim 2, residents residing in the Unite clinic building will participate in structured outcome assessments at 6 and 12 months. Risk factor reduction will be measured by change in systolic blood pressure from baseline to 12 months and change in the physical and social environment (item counts) will also be assessed from baseline to 12 months.

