### Study Population Recruitment and Enrollment

Residents of the Unite clinic building (n=300) will be recruited to complete in person, prospective observational assessments in which they will be asked structured interview questions and have their blood pressure taken. Residents will be recruited from building central locations, including community and recreation rooms, in addition to fliers, word-of-mouth, and door-to-door knocking. Recruitment will continue until all residents have been contacted and provided the opportunity to consent or decline. The housing staff will aid the research team in contacting hard-to-reach residents. Residents who do not respond to the research team and housing staff after multiple contact attempts will be considered a decline. We will use our ongoing successful retention strategies, which include maintenance of contact and obtaining alternate contact information, including those of family members, in the event of change in contact information. The assessments will take place in a private space in the Unite clinic building. Participants will be given US $20 at baseline and US $25 for each outcome assessment.

Baseline assessments will begin at the time of the Unite clinic opening, with 6- and 12-month outcome assessments. The assessments will measure resident cognition, activity limitations [40-42], blood pressure, Unite clinic usage, physical [43] and social environment [44], health-related social needs [45], and housing transition information. Blood pressure will be measured by research staff using the OMRON 7 series upper arm blood pressure monitor (OMRON Healthcare, Inc) in accordance with national standards for measurement. Housing status transition will be obtained from the Unite clinic building records including 2 years prior to the start of the Unite care model. Participant responses and blood pressure measurements will be stored in a Research Electronic Data Capture database (Vanderbilt University). Table 2 depicts which measures are assessed at each outcome assessment.

**Table 2 table2:** Comparison of aim 2 measures by outcome assessment.

	Baseline	6 months	12 months
Sociodemographics	✓		
Comorbidities	✓		
Self-rated health	✓		✓
Activity limitations	✓		
Cognitive impairment	✓		
Unite care model usage		✓	✓
Blood pressure measurement	✓	✓	✓
Physical environment	✓		✓
Social environment	✓		✓
Housing status	✓	✓	✓

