## Results

This study was funded by the National Institutes of Health-National Institutes on Aging in April 2021 and received institutional review board approval from the University of Michigan in May 2021. Semistructured interviews for aim 1 began in July 2021 and are anticipated to end in April 2023, with an anticipated total 45 stakeholders, including administrators, providers, and older adult residents. Structured interviews for aim 2 began in June 2021 and ended in November 2022. For aim 2, at baseline, 265 residents were approached, of which 179 residents enrolled. In total, 149 residents completed 6-month outcomes and 131 residents completed the final 12-month outcome. Data analysis for aim 1 is anticipated to begin in summer 2023; analysis for aim 2 will begin in spring 2023.

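### The stated primary regression uses only residents with a 12-month SBP and leaves out the 6-month SBP, although 48 of 179 enrolled (26.8%) have no 12-month outcome

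*Protocol article*

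**What the plan says.** - **Endpoint.** Data Analysis: "The primary analysis is the change in systolic blood pressure (SBP) from baseline to 12 months".
- **Model.** The same section: "Analysis will fit a linear regression model with the outcome of 12-month SBP, including baseline SBP and a binary predictor of Unite care model patient". That predictor is binary, and the model has no 6-month term.
- **Visits.** The Abstract says that "residents residing in the Unite clinic building will participate in structured outcome assessments at 6 and 12 months". In Table 2, the row "Blood pressure measurement" is ticked at baseline, 6 months and 12 months. None of the analyses described in Data Analysis takes the 6-month SBP as outcome or covariate.
- **Planned size and loss.** "we estimate that 5% will elect not to enroll, resulting in a study population of 285 older adults". With 10% loss, "we will have 89% power to detect a 2-point change in SBP within older adults"; with 20% loss, power is given as 85%.
- **Actual size and loss.** Results: "at baseline, 265 residents were approached, of which 179 residents enrolled", and "149 residents completed 6-month outcomes and 131 residents completed the final 12-month outcome". No reasons for loss are given, and no split by Unite use.
- **Timing.** Aim 2 data collection had ended in November 2022, and its analysis was to begin in spring 2023.

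**The concern.** A regression with 12-month SBP as outcome has no outcome for anyone who missed that visit. The plan considers loss only through its effect on power, and at no more than 20%. Actual loss is higher, and Unite use is observed, not assigned, so nothing in the design balances loss between users and non-users.

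Loss could plausibly be related to blood pressure. Assessments are held in person in the clinic building, so people who move or become unwell are harder to reach. The Introduction itself links hypertension to disability and nursing home admission.

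At stake is a user versus non-user contrast that partly reflects who stayed. A scheduled measurement of the primary variable, which could correct part of this, enters no stated analysis.

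**Working it through.** **1. The plan's own figures.** Inputs: 285 enrolled, a 2 mm Hg change, 10 mm Hg (printed as an SE, read here as an SD), and two-sided alpha 0.05 (assumed, not stated). For a one-sample test of mean change, power = Φ(2 / (10/√n) − 1.96).

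- 10% loss: n = 285 × 0.9 = 256.5. Power = Φ(3.203 − 1.96) = 89.3%. The plan says 89%.
- 20% loss: n = 285 × 0.8 = 228. Power = Φ(3.020 − 1.96) = 85.5%. The plan says 85%.

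Both reproduce. Loss enters only as a smaller n, which is adequate only if it is unrelated to the outcome.

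**2. Actual loss** (counts from Results).

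- No 12-month outcome: 179 − 131 = 48, and 48/179 = 26.8%.
- Lost after completing 6 months: at least 149 − 131 = 18.
- No 6-month outcome: 179 − 149 = 30. If dropout is monotone, these 30 have no follow-up SBP at all, and the 48 split as 30 + 18.

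This takes every completed assessment to include a valid SBP, which the article does not state.

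**3. When the completer regression is biased.** With monotone dropout, the 12-month use contrast can be written as

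θ12 = γ + β6 × δ6.

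Here δ6 is the use coefficient for 6-month SBP given baseline, estimated in everyone seen at 6 months. γ and β6 are the coefficients of use and 6-month SBP in the regression of 12-month SBP on baseline, use and 6-month SBP, estimated in 12-month completers. A likelihood-based repeated-measures model works in this way. The completer regression in effect takes δ6 from completers alone. If loss after 6 months depends on 6-month SBP more strongly in one use group than in the other, that δ6 is shifted, and the bias is β6 times the shift.

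**4. Size, by simulation.** All inputs are assumptions: 179 residents, no true effect, SD 15 mm Hg, visit correlations 0.55 to 0.65, and loss matched approximately to the reported counts. The log-odds of loss after 6 months rise by 0.5 to 1.5 per SD of 6-month SBP.

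| Loss after 6 months | Completer regression, bias (mm Hg) | Using 6-month SBP, bias (mm Hg) |
|---|---|---|
| Unrelated to SBP | none | none |
| Related to SBP equally in both groups | none beyond simulation noise | none beyond simulation noise |
| Related to SBP in one group only | about 0.3 to 1.05; sign depends on which group | −0.03 to 0.07 |

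**5. Precision.** Under compound symmetry with visit correlation ρ, the correlation between 6- and 12-month SBP given baseline is r = (ρ − ρ²)/(1 − ρ²). The effective n for the 12-month mean is 1 / [(1 − r²)/131 + r²/149].

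- ρ = 0.4: r = 0.286, effective n = 132.3.
- ρ = 0.7: r = 0.412, effective n = 133.7.

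Against 131, the gain is about one to three residents.

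**The case against.** **The article may simply be silent.** It does not use the term complete-case, and it does not rule out imputation with 6-month SBP as an auxiliary variable. Missing-data handling is often left to a full protocol or SAP, which is not shown. This stands to the extent that one cannot say the 6-month data will certainly be discarded. However, the article does more than omit a missing-data paragraph. It fixes the primary model, and that model as written needs a 12-month value.

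**Regression of the final value on baseline is a standard analysis.** This stands. The model is not an error and it matches the stated endpoint. The reason to reconsider is the 26.8% loss, not the form of the model.

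**The bias is hypothetical.** This also stands. It needs SBP-related loss that differs by use; the documents show no such pattern, and its sign is unknown. The simulated values are also modest beside the estimator's own SD of about 2.2 mm Hg. Expressing them as a share of the 2 mm Hg in the power statement would mislead: that figure describes change within residents, whereas the bias concerns users versus non-users.

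**The fix reaches few people.** If dropout is monotone, 18 of the 48 re-enter. Table 2 records Unite use by survey at 6 and 12 months, so survey-based use after 6 months is unknown for those 18.

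**A stronger reading to avoid.** A reader might infer that many of the 48 were lost because they moved out of the building under evaluation. The documents do not support this. Results gives counts only, moves are a separate endpoint taken from building records, and the recruitment section describes alternate contacts for people whose details change. Holding assessments in the building makes loss of movers plausible, but no number supports "many".

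**Conclusion.** The point holds in a limited form. As stated, the primary regression draws only on residents with a 12-month SBP, and the scheduled 6-month SBP has no stated role. Loss is 48 of 179 (26.8%), above both planning cases, and at least 18 of the lost residents completed the 6-month visit.

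The possible bias of about 0.3 to 1.05 mm Hg in either direction is conditional on the assumed SD, correlations and loss mechanism. It is not an estimate for this cohort. A model that uses 6-month SBP removes the bias from loss that depends on observed 6-month SBP, with no loss of precision in these simulations. It does not recover residents with no follow-up SBP, and it does not address confounding of Unite use or low power, which are separate matters. The change is worth making before analysis because it is cheap and protective. The documents do not show that the stated analysis will give a wrong answer.

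**What to change.** 1. Make the primary analysis a mixed model for repeated measures of 6- and 12-month SBP, with baseline SBP, Unite use, visit, use × visit and an unstructured covariance. Keep the 12-month user versus non-user contrast as the primary estimate, so that the question is unchanged.
2. Report the stated regression in 12-month completers as a sensitivity analysis.
3. Define Unite use the same way for every resident, for example from the clinic health record already planned for the penetration analysis, so that residents lost after 6 months can be classified.
4. Report loss at 6 and 12 months by use status.

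**Cost.** Wording in the analysis plan, slightly more analysis work, and a rule for classifying use. No new SBP data are needed. Precision barely improves, and if dropout is monotone, 30 of the 48 still contribute no follow-up SBP. The report should say so and not present the mixed model as full recovery.

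### Poisson regression is named for the environment item counts with no dispersion or robust variance; its model-based standard errors may be materially too large or too small (minor, secondary analysis)

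*Protocol article*

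**What the plan says.** The Data Analysis section for Aim 2 in the protocol article gives the model for both environment outcomes: "Change in physical and social environment (item counts) will be assessed using a Poisson regression with an outcome of 12-month values". The same sentence lists what else enters the model, namely "adjusting for baseline values and including an intervention indicator". The Methods part of the abstract describes the outcome in the same terms: "change in the physical and social environment (item counts) will also be assessed from baseline to 12 months". The endpoints are secondary: "Other secondary analysis end points will include determining whether functional and cognitive limitations are associated with care model usage, change in physical and social environment".

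The article names the model family, the outcome and two covariates. It gives no variance estimator, dispersion parameter, number of items, range, mean or variance. The instruments appear only as citations in the section on recruitment and enrolment. The Results section reports that "131 residents completed the final 12-month outcome".

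**The concern.** A Poisson model treats the outcome as an unbounded count whose variance, given the covariates, equals its mean. An item count from a fixed list departs from this in two opposing ways.

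- **Ceiling and persistence.** Each item is present or absent, so commonly endorsed items pull the variance below the mean. Features already present at baseline and still present at 12 months reduce it further once baseline is adjusted for. Model-based standard errors are then too large and power is lost.
- **Clustering.** If some residents have many items and others almost none, the variance rises above the mean. Model-based standard errors are then too small and false positives increase.

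Improvement in the physical and social environment is written into Aim 2, and a difference between users and non-users is one of the three anticipated findings. An advisory board will weigh the results. With 131 residents at 12 months against a planned 285 (131/285 = 46%), precision is already limited.

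**Working it through.** **The plan's own figures.** None exists for the item counts. The only power statement concerns blood pressure: "89% power to detect a 2-point change in SBP within older adults". It reproduces as a within-person test, with the 10 mm Hg entered as a standard deviation, two-sided 5% assumed and 285 × 0.9 ≈ 256 residents: Φ(2/(10/√256) − 1.96) = Φ(1.24) = 0.8925. It has no bearing on this point.

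**Inputs.** From the article: n = 131, Poisson model, adjustment for baseline, binary indicator. Assumed, because the article gives none of them: number of items K = 5 to 20, probability p that an item is present = 0.1 to 0.7, correlation ρ between items within a resident = 0 to 0.3, and half of residents being users.

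**Formula, before baseline adjustment.** For a beta-binomial count, variance divided by mean is φ = (1 − p)(1 + (K − 1)ρ). The ratio of Poisson to true standard error is 1/√φ.

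- p = 0.7, ρ = 0: φ = 0.30, ratio 1/√0.30 = 1.83 (83% too large).
- K = 10, p = 0.3, ρ = 0: φ = 0.70, ratio 1.20.
- K = 20, p = 0.1, ρ = 0.3: φ = 0.9 × 6.7 = 6.03, ratio 0.41 (59% too small).
- The two departures cancel (φ = 1) at ρ = p/((1 − p)(K − 1)); for K = 10, p = 0.3 this is 0.3/(0.7 × 9) = 0.048.

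**Simulation under no group effect.** 3,000 datasets per setting, n = 131, Poisson model with baseline count and group, two-sided nominal 5%. K was 5, 10 or 20; p was 0.1, 0.3 or 0.5; ρ was 0, 0.1 or 0.3. A resident's propensity to have items was either the same at both visits or unrelated between visits. Selected settings:

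| K, p, ρ | Propensity across visits | Residual dispersion | Type I, model-based | Type I, sandwich |
|---|---|---|---|---|
| 5, 0.5, 0 | same | 0.50 | 0.3% | 5.2% |
| 10, 0.3, 0 | same | 0.70 | 2.1% | 5.7% |
| 10, 0.3, 0.1 | same | 1.03 | 5.0% | 5.4% |
| 10, 0.1, 0.3 | same | 1.47 | 15.9% | 7.6% |
| 20, 0.1, 0.3 | same | 1.92 | 26.8% | 8.7% |
| 20, 0.1, 0.3 | unrelated | 5.88 | 43.1% | 6.0% |

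Over all settings, model-based error ran from 0.3% to 43%. Sandwich error was 4.2% to 6.1%, apart from the 7.6% and 8.7% above; repeat runs put that kind of setting at about 8% to 10%.

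**Persistent items.** A second set of simulations carried 50% or 80% of items over from baseline (p = 0.3 or 0.6, 40% users, 1,500 runs each). Model-based error was 2.5% or less in 34 of 36 settings. The Monte Carlo error is √(0.025 × 0.975/1,500) ≈ 0.4 points, so that tally could shift slightly. Sandwich error was 4.4% to 6.9%. Example: K = 10, p = 0.3, ρ = 0.1, 80% carried over gave dispersion 0.40, a standard error 62% too large and type I error 0.2%. In that example the critical value is 1.96 × 1.62 = 3.18 true standard errors. An effect with 80% power under correct errors (1.96 + 0.84 = 2.80 true standard errors) would have power Φ(2.80 − 3.18) = Φ(−0.38) ≈ 35%.

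**The case against.** The strongest objection is that the article is silent on the variance, and silence is not a specification. Sandwich or quasi-likelihood standard errors fit the stated text, and an article may leave that choice to a fuller plan that is not shown here. This stands. A reader might infer that the plan fixes the Poisson model's own variance, and the document does not support that reading.

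A reader might also infer that the standard errors are bound to be wrong. That is not supported either. The ceiling and the clustering can offset each other, as the 10-item setting with 5.0% error shows. Few items per resident with weak correlation would also be close to Poisson.

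The numerical inputs are all assumed, and even the ceiling is read from the words for the outcome. So the range shows what could happen and is not an estimate for this study.

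The endpoints are secondary, and the section on overall assessment describes a holistic judgment with no decision rule tied to these p-values. That limits the consequences.

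Finally, the article calls the group variable only an intervention indicator. A reader might infer that the comparison is undefined, but the Anticipated Findings section states it as residents who receive Unite care against those who do not.

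What remains is that the one model named rests on a variance assumption that this type of outcome need not meet, and nothing in the text guards against that.

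**Conclusion.** The point holds as a minor improvement to a secondary analysis. If the Poisson model's own standard errors are used, they may be materially too large (commonly endorsed or persistent items) or too small (rare, clustered items). Across the assumed scales, type I error at a nominal 5% could lie anywhere from well below 1% to above 40%, and in some settings it is about right. Size and direction for this study cannot be determined from the article. Confidence attaches to the mismatch between model and outcome type, not to any one figure. The conclusion rests on reading the outcome as a number of items from a finite list, on n = 131, and on the assumed scales.

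**What to change.** Keep the log-linear model for the 12-month count, adjusted for the baseline count, and state that inference uses robust (sandwich) standard errors. Alternatively, model items endorsed out of items asked with a quasi-binomial variance. That respects the ceiling, but with a logit link it changes the effect measure to an odds ratio, and its error rate was not simulated here.

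The cost is one sentence in the analysis plan and one software option. By the article's timeline, Aim 2 analysis had not begun when it was written. The downside is small: at n = 131, sandwich errors can be mildly anti-conservative for rare, strongly correlated items (about 8% to 10% in simulation), though in those settings the model-based errors did worse (15.9% and 26.8%).

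### The 89% and 85% power figures belong to a planned 256 and 228 completers; the article reports 131, at which the same calculation gives about 62%

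*Protocol article*

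**What the plan says.** All references are to the protocol article.

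- **Data Analysis, planned enrolment:** "we estimate that 5% will elect not to enroll, resulting in a study population of 285 older adults".
- **Data Analysis, stated power:** "We estimate that we will have 89% power to detect a 2-point change in SBP within older adults". The inputs are a variability described as "SE of change in SBP over time of 10 mm Hg" and "a 10% loss to follow-up using an analogous test to our primary analysis".
- **Data Analysis, higher loss:** "If loss to follow-up increases to 20%, power to detect a 2-point change in SBP would decrease to 85"%. For a larger effect: "We will have 100% power to detect a 4-point SBP change if loss to follow-up were 20"%.
- **Data Analysis, primary model:** a linear regression of 12-month SBP on baseline SBP and an indicator of being a Unite patient or not.
- **Results, realised sample:** "265 residents were approached, of which 179 residents enrolled", and "149 residents completed 6-month outcomes and 131 residents completed the final 12-month outcome". Aim 2 collection ended in November 2022, with analysis to start in spring 2023.

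The article does not restate power or precision for the realised sample. Strengths and Limitations mentions recruitment and retention only as possible difficulties.

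**The concern.** Both planning inputs had already failed when the article was written, and the article itself reports the numbers that show it. Uptake was far below 95%, and loss to 12 months went past the 20% that the sensitivity figure allows for. A reader who goes from the power paragraph to the eventual SBP result will take 85% as the lower end of what the study could deliver.

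The article presents 2 mm Hg as clinically meaningful. A non-significant SBP coefficient set beside 85% to 89% power would look like good evidence against a benefit of that size. With 131 completers it would be much weaker evidence than that.

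**Working it through.** **Inputs from the article.** Residents 300; planned enrolment 285; loss 10% or 20%; effect 2 mm Hg; variability 10 mm Hg; approached 265; enrolled 179; 12-month completers 131.

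**Assumptions.** Alpha and sidedness are not stated; two-sided 0.05 is used. The 10 mm Hg is called an SE but reproduces the stated powers only as the SD of individual change. The share of users is not given; 50% and 30% are shown, with 10% as a low extreme. The residual SD of the regression is not given; 10 mm Hg is used.

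**1. Reproduce the stated figures.** One-sample test of mean change, power = Φ(δ√n / SD − 1.96).
- 10% loss: n = 285 × 0.90 ≈ 256. Φ(2 × 16 / 10 − 1.96) = Φ(1.24) = 89.3%; noncentral t gives 89.0%. Stated: 89%.
- 20% loss: n = 285 × 0.80 = 228. Φ(2 × 15.10 / 10 − 1.96) = Φ(1.06) = 85.5%; noncentral t gives 85.3%. Stated: 85%.
- 4 mm Hg at n = 228: above 99.9%. Stated: 100%.

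One-sided 0.05 gives 94% and 91%, which do not match. A two-group test for 2 mm Hg does not match at any user share from 10% to 50%; its highest two-sided value at 256 is 36%.

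**2. Compare plan and outcome.**
- Not enrolled: (265 − 179) / 265 = 86 / 265 = 32.5% of those approached, against 5% assumed.
- Lost by 12 months: (179 − 131) / 179 = 48 / 179 = 26.8%, against 10% assumed and 20% as the higher case.
- Completers: 131 / 256 = 51% of plan; 131 / 228 = 57% of the 20%-loss case.

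**3. Same test at the achieved size.** Φ(2 × 11.45 / 10 − 1.96) = Φ(0.33) = 62.9%; noncentral t gives 62.3%. The effect detectable with 80% power is (1.96 + 0.84) × 10 / √131 ≈ 2.45 mm Hg. For 4 mm Hg, power is still 99.5%.

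**4. The planned between-group model.** SE = 10 × √(1/n₁ + 1/n₂); power ≈ Φ(δ/SE − 1.96); half-width = 1.96 × SE; detectable difference at 80% power = 2.80 × SE.

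| n | Users | SE | Power, 2 mm Hg | 95% CI half-width | Detectable at 80% |
|---|---|---|---|---|---|
| 256 | 50% | 1.25 | 36% | 2.4 | 3.5 |
| 131 | 50% | 1.75 | 21% | 3.4 | 4.9 |
| 131 | 30% | 1.91 | 18% | 3.7 | 5.3 |

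At 131 with 10% users, power for 2 mm Hg is about 10%.

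**5. Separate the two causes.** At an equal split, moving from the one-sample test to the between-group model takes power from 89% to 36% at the planned size. The shortfall in completers then takes it from 36% to 21%. On the one-sample test alone, the shortfall takes it from 89% to 62%.

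**The case against.** The strongest reply is that a power statement is a design-stage forecast. It is marked as an estimate, its arithmetic is correct, the Methods are written in the future tense throughout, and the Results section openly gives the realised counts. Data collection is closed, so no design decision can change, and the eventual confidence interval will show the precision whatever is restated. This stands as far as it goes. A reader might infer that 89% and 85% were miscalculated; they were not. What remains is that one article carries both the forecast and the counts that overturn it without connecting them, at a time when analysis has not begun. Restating precision from the achieved size and the planning SD is not post hoc power from an observed effect.

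Other stronger readings are also tempting, and the article does not support them:
- **That 131 completers cannot exclude a 2 mm Hg benefit.** This depends on the estimate. On the one-sample test the half-width is 1.96 × 10 / √131 = 1.7 mm Hg, so an interval centred on zero would exclude 2. In the between-group model, an estimate more than about 1.4 mm Hg (3.4 − 2) to 1.7 mm Hg (3.7 − 2) in the unfavourable direction would exclude it.
- **That poor recruitment cut power from 89% to about 20%.** Most of that drop is the mismatch between test and model, a separate matter.
- **That the advisory panel will judge the SBP result against the stated power.** The section on overall assessment does not mention power and says that no single metric is likely to suffice.
- **That 149 residents have some follow-up.** That is the 6-month count only.

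The one-sample test is itself an inference, since the text says only that the test is analogous to the primary analysis. The residual SD of 10 is conservative at a given split, because adjustment for baseline SBP cannot leave more residual variation than the change score.

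**Conclusion.** The point holds as a reporting defect with a real consequence for interpretation. The stated 89% and 85% are valid for 256 and 228 completers. The study has 131, and on the test that reproduces those figures power for 2 mm Hg is about 62%. This rests on two-sided 0.05 and on 10 mm Hg being an SD of change. At one-sided 0.05 it would be about 74%, still below 85%, but that convention does not reproduce the plan.

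For the model that will be fitted, power for 2 mm Hg is about 18% to 21% with 30% to 50% users and residual SD 10. About 36% is what the full planned sample would have given at an equal split. The claim about 4 mm Hg is hardly affected on the one-sample test. The study is therefore less informative about a 2 mm Hg difference than its power paragraph suggests, but this does not mean that it can say nothing about one.

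**What to change.** Before the aim 2 analysis:

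1. Keep 89% and 85% only as planning figures, labelled as superseded by the realised enrolment and follow-up.
2. State the achieved 12-month sample of 131 beside them, with the 26.8% loss.
3. Give the attainable precision for the user-versus-non-user coefficient: a 95% CI half-width of about 3.4 mm Hg with 50% users and 3.7 mm Hg with 30%. State the assumed residual SD of 10 mm Hg and the two-sided 0.05 level, and replace the assumed share with the actual one once it is known.
4. Add a sentence that a non-significant or near-zero coefficient would not by itself rule out a 2 mm Hg benefit.

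The cost is text only. No data, visits or models change, and the stated figure becomes less favourable.

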## Discussion

### Anticipated Findings

We anticipate the following outcomes: (1) among older adults residing in the Unite clinic building, those with functional and cognitive limitations (ie, activity limitations, AD/ADRD) will be more likely to use the Unite care model than those without limitations; (2) among older adults residing in the Unite clinic building, those who receive care through the Unite care model will have reduced SBP compared to those who do not receive care through the Unite care model; and (3) Among older adults residing in the Unite clinic building, those who receive care through the Unite care model will have an increase in physical environment modifications and a decrease in social isolation compared to those who do not receive care through the care model.

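### The stated 89%, 85% and 100% power belong to a one-sample before-after test, not to the Unite-patient coefficient that is the primary analysis, whose power for 2 mm Hg is far lower under any plausible user share

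*Protocol article*

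**What the plan says.** Under Data Analysis (Aim 2), the protocol article names change in SBP from baseline to 12 months as the primary analysis and then specifies the model: "Analysis will fit a linear regression model with the outcome of 12-month SBP, including baseline SBP and a binary predictor of Unite care model patient". Anticipated Findings gives the matching hypothesis, that "those who receive care through the Unite care model will have reduced SBP compared to those who do not receive care" through the model.

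The power paragraph in the same Data Analysis section starts from 300 residents: "we estimate that 5% will elect not to enroll, resulting in a study population of 285 older adults". It then says "We estimate that we will have 89% power to detect a 2-point change in SBP within older adults", taking "SE of change in SBP over time of 10 mm Hg", a 10% loss to follow-up and "using an analogous test to our primary analysis". With 20% loss it gives 85% for 2 points and 100% for 4 points. It states no user share, no correlation between baseline and 12-month SBP, and no significance level.

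The Results section reports the sample achieved: 179 residents enrolled and 131 completed the 12-month assessment.

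**The concern.** The model and the hypothesis compare users with non-users. The power statement concerns change within the whole group and uses the whole expected sample. Power for a group coefficient depends on how the sample divides between the groups, and no split is given, so the quoted figures appear to belong to a different test.

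What is at stake is how an SBP result is read. A reader told that the study had 85% to 89% power for 2 mm Hg could take a non-significant Unite-patient coefficient as good evidence against a benefit of that size. If the real power is well below one half, that inference fails.

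**Working it through.** **Inputs from the Data Analysis section.** Enrolled: 300 × 0.95 = 285. Analysed at 10% loss: 285 × 0.90 = 256.5, taken as 256. Analysed at 20% loss: 285 × 0.80 = 228. Difference: 2 or 4 mm Hg. Variability of change: 10 mm Hg. **From Results:** 131 completers at 12 months.

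**Assumptions, not in the article.** Two-sided 5%; user share p from 20% to 50%; correlation r of 0.5 or more, with r = 0 shown as a limit; equal SBP variance at baseline and 12 months.

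**Step 1. Reproduce the stated figures.** One-sample test of mean change, power = Φ(δ / (10/√n) − 1.96):

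- n=256, δ=2: SE = 10/16 = 0.625; 2/0.625 = 3.20; Φ(1.24) = 89.3% (noncentral t: 89.0%). Stated: 89%.
- n=228, δ=2: SE = 0.662; ratio 3.02; Φ(1.06) = 85.5% (noncentral t: 85.2%). Stated: 85%.
- n=228, δ=4: ratio 6.04; above 99.99%. Stated: 100%.

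All three match. Other tests do not give 89%: one-sided one-sample 94.0%; two groups at an even split, two-sided 35.9% or one-sided 48.2%; 256 per group 61.9%.

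**Step 2. SE or SD.** The 10 mm Hg enters Step 1 as the SD of individual change. If 10 were the SE of the mean change, 2/10 = 0.2 and power would be about 5%.

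**Step 3. The stated coefficient.** SE = s × √(1/(np) + 1/(n(1−p))), where s is the residual SD. With SD of change 10, baseline adjustment gives s = 10 × √((1+r)/2): 10 as r approaches 1 (no gain over change scores), 8.66 at r=0.5 and 7.07 at r=0.

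Example, n=256, even split, s=10: SE = 10 × √(1/128 + 1/128) = 1.25; 2/1.25 = 1.60; Φ(1.60 − 1.96) = 35.9%.

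Results by noncentral t with n−3 degrees of freedom (the normal formula agrees to within one percentage point):

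| Case | 50% users, s=10 | 50% users, r=0.5 | 20% users, s=10 | 20% users, r=0.5 |
|---|---|---|---|---|
| 2 mm Hg, n=256 (stated 89%) | 36% | 45% | 25% | 31% |
| 4 mm Hg, n=228 (stated 100%) | 85% | 94% | 67% | 79% |
| 2 mm Hg, n=131 | 21% | 26% | 15% | 18% |

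At the limit r=0 with an even split, power for 2 mm Hg at n=256 is 62%.

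**Step 4. Detectable difference.** At 80% power and n=131 this is (1.96 + 0.84) × SE. The SE runs from 1.513 (50% users, r=0.5) to 2.184 (20% users, s=10), giving 4.2 to 6.1 mm Hg.

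**Step 5. What would restore 89%.** At n=256 and an even split the SE must be 2/(1.96 + 1.23) = 0.63. Since SE = s/8 there, s must be about 5.0, half the stated variability. That is below the 7.07 reached at r=0.

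**The case against.** *The primary analysis is simply change over time.* The opening sentence of Data Analysis allows that reading, and the power sentence does speak of change within older adults. The arithmetic is right for that test. But the model specified, "including baseline SBP and a binary predictor of Unite care model patient (yes vs no) as independent variables", and the stated hypothesis are both between-group. If before-after change were intended, the model would be the part to correct. The two have to be reconciled either way.

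*Baseline adjustment recovers the power.* It helps, and this part stands. One might infer that the group coefficient has at least four times the variance of the one-sample mean. That is true of unadjusted change scores, but not of this model: at an even split the ratio is 4 × (1+r)/2 = 2(1+r), which is below four for any r<1. Even so, r=0 gives only 62%.

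*The 10 mm Hg might be the SD of a single reading.* Then s = 10 × √(1−r²), and r of about 0.86 to 0.87 would reach 89% at an even split. The text, however, describes it as variability of the change over time.

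*Nothing turns on one p-value.* This also stands. A reader might infer that a null SBP coefficient would count decisively against the care model. Overall Assessment of Unite Care Model instead describes a holistic judgment by the advisory board that rests on no single metric. The risk is a misread input to that judgment, not a failed decision rule. Follow-up has closed as well, so the correction affects interpretation rather than design.

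**Conclusion.** The mismatch is established: the three figures fit a one-sample before-after test, and no reading of the stated inputs gives 89% for the Unite-patient coefficient. Calling the test analogous to the primary analysis is wrong.

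The size is conditional. With 10 mm Hg as the SD of change, two-sided 5%, 20% to 50% users and r of 0.5 or more, power is about 25% to 45% for 2 mm Hg at n=256, about 67% to 94% for 4 mm Hg at n=228, and about 15% to 26% for 2 mm Hg at n=131.

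It is tempting to say that true power is 36%. The documents do not support a single figure: 36% assumes an even split and no gain from baseline adjustment, and the article gives neither the user share nor r. An even split is the most favourable one, and a share below 20% would push power under the ranges shown.

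**What to change.** Replace the power paragraph with power, or the minimum detectable difference, for the Unite-patient coefficient in the stated regression. Show it over a range of user shares and r, at the planned sample sizes and at n=131, with the significance level stated. Change SE to SD of change. Keep 89% and 85% only if they are labelled as applying to a separate, uncontrolled before-after analysis at the planned sample size. Add a sentence for the advisory board that a null SBP coefficient cannot rule out a 2 mm Hg benefit.

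The cost is one rewritten paragraph and no new data. The drawback is that the stated power becomes much less favourable.
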